## Data Management and Analysis

Data will be entered into Epidata version 3.1 and exported to STATA version 16 for analysis. The entered data will be cleaned and recoded before analysis. If there is any missing data, multiple imputation methods will be used to manage the missing data.

Before performing the main analysis, data will be weighted using the sample selection probability and the weighting class adjustment method to control for selection bias and non-response bias respectively ([147](#_ENREF_147), [148](#_ENREF_148)) based on the auxiliary data collected for the Demographic and Health Survey by Hawassa University.

The nature of the data and its distribution will be checked to identify any special distribution. For categorical data, its frequency will be run and checked for any unusual distribution. For continuous data, both statistical methods (mean, standard deviation, median, Skewness, and kurtosis); and graphical presentations (histogram) will be used to check its normal distribution. A mean and standard deviation will be reported for normally distributed data, while the median and interquartile ranges will be reported for non-normally distributed data.

The primary outcome in this study is the presence of anatomical pelvic organ prolapse, which is pelvic organ prolapse of stage I or more prolapse diagnosed through pelvic examination.

To identify predictors of POP, initially, data stratification will be done to identify possible confounders and effect modifiers ([149](#_ENREF_149)). Variable are considered confounding when their crude result (unadjusted odds ratio) is different from Mantel-Haenszel (M-H) (adjusted odds ratio) on stratified data ([150](#_ENREF_150)). An effect modifier is considered when the odds ratio of a variable is different across the strata.

In addition, the multicollinarity of the independent variables will be checked before the variable is fitted into multivariable logistic regression. In the multiple linear regression model, the variance inflation factor (VIF) > 1 and tolerance statistics < 0.1 show the presence of multicollinarity. The variance inflation factor (VIF) of 1-5 shows moderate multicollinarity, while VIF >5 shows high multicollinarity. In this analysis, variables with high multicollinarity will be omitted from the analysis ([151](#_ENREF_151)).

Finally, bi-variable and multivariable logistic regression analysis will be done using complex sample survey analysis to control for possible confounding and identify predictor factors ([149](#_ENREF_149)). In bi-variable logistic regression analysis, variables with a P-value < 0.25 will be fitted into multivariable logistic regression in a stepwise fashion ([152](#_ENREF_152)) using the ENTER method. In multivariable logistic regression, a variable is identified as a predictor factor for POP if the 95% confidence interval of the adjusted odds ratio does not include 1 and the P-value <0.05. The model parameter is estimated by pseudo maximum likely hood estimation that accounts for the features of a complex sample design. A Archer and Lemeshow goodness-of-fit test that accounts for the effect of sampling design and weight will be used also ([153](#_ENREF_153)).

The Principal Component Analysis (PCA) will be carried out for the computation of the wealth index. The PCA will be done in a series of steps. Initially, the continuous variables will be standardized so that each one of them contributes equally to the analysis. Then covariance matrix computation will be done to identify correlations and compute the eigenvectors and eigenvalues of the covariance matrix to identify the principal components (new variables). Then a feature vector will be created to decide which principal components to keep. Finally, recast the data along the principal component axes ([154-156](#_ENREF_154)). All the variables are dichotomized and the scores are derived using principal component analysis and ranked in three quintiles ([142](#_ENREF_142)). Lowest quintile: those who score below the 3^rd^ quintile in wealth index ranking. Middle quintile: those who score the middle 3^rd^ quintile in wealth index ranking. Highest quintile: those who score the upper 3^rd^ quintile in wealth index ranking.

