## Variables

The outcome variable of this study is a change in Pelvic Organ Prolapse Symptom as measured by POP-SS and the intervention is Pelvic Muscle Training. Covariates include degree of POP, the severity of POP-SS, adherence to Pelvic Floor Muscle Training protocol, maternal age, location of POP, history of pelvic surgery, number of childbirth, level of education, body mass index, trauma, marital status, occupation, age at first marriage, age at first delivery, place of delivery, history of prolonged labor, medical conditions (chronic cough, diabetes mellitus), family history of POP, mode of delivery, duration since last menstrual period.

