## Data Management and Analysis

Data entry, cleaning, missing data management and descriptive data presentation is similar with Paper-II. In addition, in this paper, to assess the effect of pelvic floor muscle training on prolapse symptoms, an Intention-to-treat (ITT) analysis will be used at the end of six months of training. This analysis will include all women included in the trial study at the beginning and who attended at least one follow-up. A paired t-test will be used to evaluate the mean change from baseline for both groups (intervention and control) groups. Then independent t-test will be used to compare the mean change for the interventional groups against the mean change of the control group as an effect size. The level of significance will be set at a P-value < 0.0125 by using the Bonferroni correction formula for multiple outcomes (16, 29, 30). In this study, there are four outcomes of this single intervention, which included a mean change in prolapse symptoms and three components of prolapse quality of life (Paper IV). Therefore, the level of significance is obtained by dividing the usual P-value (0.05) by a number of statistics to be performed.

A summary of statistics will be computed both at the cluster-level and individual levels for both arms. The presence of cluster effects will be assessed and a multilevel analysis will be considered if a significant ICC value of > 0.5 is detected (31). As an alternative, since the outcome of this study is continuous data, both the cluster-level and individual-level analysis will produce the same result if the cluster size is equal. But if the cluster size is variable, an individual-level analysis weighted by cluster size will be done (20, 21).

This study will use stratified cluster randomization based on geographical locations. This may not balance all possible confounders, especially individual-level factors that may vary across strata. Therefore, the statistical technique of confounder control will be used to control possible confounders at the analysis stage. A Linear Mixed-Effect Model will be used to control confounders in multivariable linear regression. This analysis can increase the statistical power and preferable than the general equation estimation model (GEE) (32). Multicollinarity of the independent variables will be checked before fitting the variable into multivariable linear regression in similar fashion with Paper-II.

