## Data Management and Analysis

The Data management and analysis procedure is similar with paper-III. In addition to that, a paired t-test will be used to evaluate the mean change of the three components of P-QoL from baseline for both groups (intervention and control) groups. Then an independent t-test will be used to compare the mean change for interventional groups against the mean change of the control group as the effect size for all the three components separately. The level of significance will be set at a P-value < 0.0125 by using the Bonferroni correction formula for multiple outcomes (16, 29, 30).

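### The multicollinearity rule contradicts itself on its threshold and omits every variable with VIF above 5, protecting neither confounders nor, in the trial's adjusted models, the arm term

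*Protocol*

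**What the plan says.** The rule stands in the Protocol, Paper II, Data Management and Analysis. It first gives a test for whether multicollinearity exists: "the variance inflation factor (VIF) > 1 and tolerance statistics < 0.1 show the presence of multicollinarity". It then grades it: "The variance inflation factor (VIF) of 1-5 shows moderate multicollinarity, while VIF >5 shows high multicollinarity". The action follows: "In this analysis, variables with high multicollinarity will be omitted from the analysis". No order of removal is given and no variable is exempted.

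The trial takes over the rule. Paper-III, Data Management and Analysis, says of the adjusted linear model: "Multicollinarity of the independent variables will be checked before fitting the variable into multivariable linear regression in similar fashion with Paper-II". Paper-IV, same heading, adds: "The Data management and analysis procedure is similar with paper-III". The covariates in Paper-III, Variables, include "adherence to Pelvic Floor Muscle Training protocol, maternal age, location of POP", and Paper-IV, Variables, also lists adherence. Under Description of Intervention, the control group gets lifestyle advice but no muscle training.

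The stated comparison between arms in Papers III and IV is an independent t-test on mean change. The mixed model comes afterwards, to deal with confounders that stratified randomisation may leave unbalanced.

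**The concern.** There are two separate problems.

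First, the statements about when collinearity is present cannot all be true, because tolerance and VIF are the same quantity inverted.

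Second, the consequence is automatic deletion. The multivariable model in Paper II exists to control confounding. Its candidate list contains groups of variables likely to be related: age, duration of menopause, age at first marriage, age at first delivery and number of births. Deleting a confounder because it correlates with other predictors returns the confounding it was there to remove, so the remaining odds ratios may be biased.

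In the trial, adherence to the training is tied to the arm by design. If both enter the adjusted model, each can flag the other. The rule does not say that the arm term, whose coefficient is the purpose of the model, must stay.

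**Working it through.** **1. Thresholds on one scale.** Tolerance = 1/VIF = 1 − R², where R² comes from regressing the predictor on the other predictors.

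| Statement in the protocol | As VIF | As tolerance | As R² |
|---|---|---|---|
| Presence, VIF part | > 1 | < 1 | > 0 |
| Presence, tolerance part | > 10 | < 0.1 | > 0.90 |
| High, leads to omission | > 5 | < 0.2 | > 0.80 |

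Read jointly, the presence test reduces to VIF > 10. A predictor with VIF 6 has tolerance 1/6 = 0.17, so it fails that test but is graded high and omitted. A predictor with VIF 3 is moderately collinear in one sentence and not collinear in the other.

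Read alone, VIF > 1 separates nothing. In 500 simulated data sets of 155 women with 15 mutually independent predictors, all 15 exceeded 1 every time. The largest VIF averaged 1.18, so the omission cut of 5 was far off.

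**2. Reach in Paper II.** With a single correlate, VIF = 1/(1 − r²).
- r = 0.8: 1/(1 − 0.64) = 2.8.
- r = 0.9: 1/(1 − 0.81) = 5.3.
- The cut of 5 corresponds to r² = 0.80, so r of about 0.89.

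With two predictors the VIF is the same for both, so the rule as worded names both. The protocol gives no correlations, so whether age or number of births would reach the cut is unknown.

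**3. Reach in the trial.** Assumptions not given in the protocol: equal arms, adherence set to 0 in controls, and mean m and standard deviation s in the trained arm. Then

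r² = 0.25m² / (0.25m² + 0.5s²), so VIF = 1 + m²/(2s²), for arm and adherence alike.

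| Adherence in trained arm (assumed) | Calculation | VIF |
|---|---|---|
| mean 60%, SD 25% | 1 + 0.36/0.125 | 3.9 |
| mean 75%, SD 20% | 1 + 0.5625/0.08 | 8.0 |
| mean 80%, SD 15% | 1 + 0.64/0.045 | 15.2 |

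Paper-III, Data Measurements, also defines adequate adherence as at least 80% of sessions. If that binary indicator is entered and a proportion a of trained women is adequate, s² = a(1 − a) and VIF = (2 − a)/(2 − 2a).
- a = 0.80: 1.2/0.4 = 3.0.
- VIF = 5 requires 2 − a = 10 − 10a, so a = 8/9 = 88.9%.
- a = 0.95: 1.05/0.10 = 10.5.

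These values are for arm and adherence alone; further covariates cannot lower them. Under either coding, good and uniform adherence brings the rule into play.

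**The case against.** The strongest reply is that the inconsistency does not change what gets deleted. VIF above 1, 1 to 5 and above 5 form one graded scale, and only the tolerance figure is out of line with it. Omission attaches to the high grade alone. That is correct: a reader might infer three incompatible triggers for deletion, but the text supports one, VIF above 5.

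Some further inferences also go too far.
- **Both members of a correlated pair must go.** The wording allows this, but dropping one and rechecking is equally compatible with it. The fault is that the protocol does not say which.
- **A parity 4+ category would be deleted through its coding.** A dummy with share p has VIF (1 − p)(p + p0)/p0, where p0 is the reference share. At p of 40-60% this gives 5.2-5.5 if 5% are nulliparous, but 2.8-3.0 if 10% are. That category appears only in the sample-size table. The Paper II variable list and the questionnaire give the number of births, a count, which has no such dummy.
- **The rule deletes the treatment effect under test.** Paper-III, Variables, lists the intervention apart from the covariates and does not name it for removal. Loss of the arm term needs adherence in the same model, coded zero in controls, at high levels. Even then the t-test stands.

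It can also be said that VIF above 5 is a conventional screen and that model-building detail belongs in an analysis plan. That excuses detail left out. Here the protocol states the rule, and states it inconsistently. Whether adherence, measured after randomisation, should be a covariate at all is a separate question, which a change to the VIF wording does not settle.

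**Conclusion.** The concern holds in limited form. The contradiction between tolerance below 0.1 and the VIF grading is a matter of arithmetic and needs no assumption. The lack of any protected variable or order of removal is plain from the text, as is its transfer to Papers III and IV.

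The consequences are conditional. Loss of age or parity in Paper II depends on correlations the protocol does not give. In the trial, the arm term has VIF 3.9 to 15.2 over the assumed continuous adherence values, and one of those three scenarios stays below the cut. With the binary definition it passes 5 only when more than about 89% of trained women are adequate. Only the adjusted estimates are exposed. The t-test comparisons and the sample size, power and significance level are untouched. The point merits a correction because the change is specific and removes a route to bias in the adjusted results.

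**What to change.** In Paper II, Data Management and Analysis:
1. Delete the sentence combining VIF above 1 with tolerance below 0.1, or restate it so that one threshold applies throughout (VIF 5 is tolerance 0.2; VIF 10 is tolerance 0.1).
2. Replace automatic omission with a diagnostic: report VIF and use it to interpret wide intervals, not to select variables.
3. Where two covariates carry the same information, such as age at first marriage and age at first delivery, or age and duration of menopause, name in advance the one to keep, on subject-matter grounds.
4. State that prespecified confounders such as age and parity are never omitted on VIF grounds.

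In Papers III and IV, add that arm and baseline score are likewise never omitted on VIF grounds.

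The cost is wording only. Some adjusted standard errors may be slightly wider because correlated confounders stay in the model.

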# **PHASE-II PROJECT**

# **PAPER-III**

Effect of Pelvic Floor Muscle Training for reducing Pelvic Organ Prolapse Symptoms in Sidama National Regional State, Ethiopia, 2022.

## Objective

1. To evaluate the effect of Pelvic Floor Muscle Training for reducing prolapse symptoms in Sidama Region, Ethiopia.

## Study Area and Period

The study area is the same as for paper II. Study time will follow immediately after study I and continued for six months. Therefore, this study will be conducted from July – to December 2022.

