**Methods:** This study will be conducted in two phases. Initially, the pelvic organ prolapse Symptom Score questionnaire will be translated into Sidaamu Afoo and evaluated for its psychometric properties on a sample of 70 women with pelvic organ prolapse recruited from the gynecology outpatients of Adare General Hospital and Yirgalem Hamline Fistula Center from May 1-25, 2022. Then a complex sample survey will be conducted to establish the prevalence of prolapse based on a sample size of 816 women. It will be conducted in eight kebeles of the Dale and the Wonsho districts from June 1–July 30, 2022. A multistage stratified sampling technique will be used to recruit study participants. The data will be collected through face-to-face interviews with the selected women at the household level. Then all women will be invited to have a pelvic examination at a nearby health facility where the prevalence of the prolapse will be determined by pelvic examination. A complex sample survey analysis will be used to determine the prevalence and determinants of pelvic organ prolapse. In the second phase of the project, a cluster-randomized controlled trial study will be conducted to evaluate the effect of pelvic floor muscle training for the reduction of prolapse symptoms and improving quality of life among 136 (68 participants in each arm). The health-related quality of life will be assessed by using a translated Sidaamu Afoo version of the Prolapse Quality of Life tool, validated in the Amharic version. A Student t-test will be used to evaluate the mean change between the two groups (control and intervention), both for prolapse symptoms and quality of life separately. Linear Mixed-effect Model will be used to control potential confounders in multivariable linear regression for both outcomes.

**Work Plan and Budget**: This study will be conducted from April to November 2022. A total of **762, 295** Ethiopian Birr **($15,245.9)** is needed to conduct this study.

**Key terms:** Ethiopia, Pelvic Organ Prolapse, prolapse, POP, quality of life, pelvic floor muscle exercise, PFMT, pelvic muscle training

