At the initial visit, they will be given a diary where they record (tally) the duration and frequency of exercise they practiced. In case they cannot make a tally, a different color and size of buttons will be provided (larger black buttons represent a number of days per week they perform the training, medium red buttons represent the frequency of training performed per day and the white small buttons represent the number of contractions performed). They will put buttons in a given box each day they perform the training and this will be checked on each visit. To ensure participants' follow-up, the respective pelvic muscle trainer will remind them two days before the appointment day through women’s phone or their respective Health Extension workers. In addition, transportation costs and time compensation will be covered by the research team. In a case where the participant cannot attend the visit, the PFM trainer will visit her at home. The change in prolapse symptoms will be analyzed at six months.

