## Data Measurements

At each visit, women's adherence to pelvic floor muscle training will be evaluated by their pelvic muscle trainer. At week two, women will be assessed for adherence to pelvic floor muscle exercise in the last two weeks (three times a day, once a day, a more than once per week, once per week, a more than one days per week). At weeks six, 10, and 15, they will be assessed for adherence to pelvic floor muscle exercise in the last four weeks using similar questions used on week two (three times a day, once a day, a more than once per week, once per week, a more than one day per week). In addition, they will be assessed for prolapse symptoms at weeks 10 and 15.

At the end of six months, the overall adherence to training protocol will be evaluated from their dairy or report of pelvic muscle trainer. Women’s adherence to training protocol is considered adequate when they complete at least 80% of the training sessions (24). This will be calculated at each visit based on the training session and finally compiled.

The primary outcome of the study is a change in prolapse symptoms measured by POP-SS. The POP-SS is the same measurement with study one which measures the frequency of prolapse symptoms in the last four weeks, measured by seven items with a Likert-scale of 0 to 4 scale (0= never felt symptom, 1= occasionally, 2= sometimes, 3= most of the time and 4= all of the time). The total score will be calculated by summing up all responses for the seven-question and the total score will range from 0 to 28, the highest value indicating the severity of prolapse symptoms (25, 26). At the end of the six months, the mean change in prolapse symptoms from the initial visit will be compared between the two groups (intervention and control groups) to measure the effect of pelvic muscle training.

The secondary outcome, women’s perceived change in prolapse symptom since the start of the intervention, will be measured as improved, the same, or worsened based on Patient Global Impression of Change (PGIC) (14, 27).

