Data collection will be conducted in two phases. The baseline data will be collected from 130 symptomatic POP stage I-III participants at the health facility immediately as soon as they are diagnosed with POP (Paper-II). The data will be collected through face-to-face interviews by the same person who perform pelvic examination from 01 June – 24 July 2022. The end-line data will be collected after six months of intervention. The data will be collected at the household level by data collectors who know the house of these participants. These data collectors will be those who collected the data at the beginning of the study (Paper-II).

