# **BUDGET**

Table 5: Budget Breakdown for the study conducted on Pe/vic Organ Prolapse in Sidama Region, Ethiopia, 2022.

| S. no | Item | Unit | Quantity | Cost/unit (ETB) | Multiplication | Total in ETB and (American Dollar) |
| --- | --- | --- | --- | --- | --- | --- |
|  | Ethical clearance | Proposal | 01 | 300 |  | 300 ($6) |
|  | Tool translation | Person | 02 | 359 | 5days | 3590($71.8) |
|  | Questionnaire duplication | Page | 20 | 2 | 857 | 34,280($685.6) |
|  | Data collection training | Person | 20 | 359 | 05 days | 35,900 ($718) |
|  | Hall rent | Room | 01 | 1000 | 03 days | 3000 ($60) |
|  | Refreshment | Person | 20 | 150 | 03 days | 9,000 ($180) |
|  | Transportation | Person | 20 | 100 | 2 round | 4000 ($80) |
|  | Trainer perdiem | Person | 02 | 1500 | 03 days | 9000 ($180) |
|  | Data collector perdiam | Person | 16 | 359 | 10 days | 57,440 ($1,149) |
|  | Women transportation | Person | 816 | 300 |  | 244,800 ($4,896) |
|  | Pelvic examiner | Person | 2 | 1500 | 30 days | 90,000 ($1,800) |
|  | Tool validation | Person | 2 | 300 | 50patient | 30,000 ($600) |
|  | Mask and Sanitizer | Person | 15 | 100 |  | 1500 ($30) |
|  | Speculum rent | Each | 816 | 20 |  | 16,320($326.4) |
|  | Sub-total 1 |  |  |  |  | **539,130 ($10,782.6)** |
|  | **PHASE**-II | | | | | |
|  | PFMT trainer | Person | 4 | 1000 | 10 days | 40,000 ($800) |
|  | Follow-up transportation | Person | 136 | 200 | 4 round | 108,800 ($2,176) |
|  | End line assessment | Person | 8 | 359 | 5 days | 12,565 ($251.3) |
|  | Supervisor per diam | Person | 02 | 359 | 40 days | 28,720 ($574.4) |
|  | Data entry (clerk) | Person | 02 | 359 | 10 days | 7,180 ($143.6) |
|  | Mobile card | Person | 15 | 200 |  | 3000 ($60) |
|  | Glove | Pack | 18 | 800 |  | 14400 ($288) |
|  | Spatula | Pack | 09 | 500 |  | 4500 ($90) |
|  | Pen and note pad | Each | 100 | 40 |  | 4,000 ($80) |
|  | Sub-total 2 |  |  |  |  | **223,165 ($4,463.3)** |
|  | Ground total |  |  |  |  | **762, 295 ($15,245.9)** |

****** $1 = 50 Ethiopian birr

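### The stated trial period, July to December 2022, ends before the last women can reach the six-month primary time point

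*Protocol*

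**What the plan says.** **Trial period.** Paper III, Study Area and Period, gives a start rule and a length: "Study time will follow immediately after study I and continued for six months". From these it concludes: "Therefore, this study will be conducted from July – to December 2022". Paper IV adopts the same period. The Summary, under Work Plan and Budget, is shorter: "This study will be conducted from April to November 2022".

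**Baseline.** Trial participants are the women found to have symptomatic prolapse in Paper II. Paper II (Study Setting and Period) and Paper IV (Data Collection Tools and Procedures) date the survey and the trial baseline 1 June to 24 July 2022. The Summary dates the survey 1 June to 30 July. Paper II, Data Collection Tools and Procedures, places the household interviews in April to June 2022.

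**Time point.** Paper III, Description of Intervention: "The change in prolapse symptoms will be analyzed at six months". Data Measurements: "At the end of the six months, the mean change in prolapse symptoms from the initial visit will be compared between the two groups". Data Management and Analysis: "an Intention-to-treat (ITT) analysis will be used at the end of six months of training". Paper IV: "The end-line data will be collected after six months of intervention". Paper III's own data collection section also places the end-line interview after six months of intervention.

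**The concern.** The stated period is presented as following from the start rule and the length, and it does not. A trial that begins when a late-July survey ends and lasts six months finishes in late January, not December, and still less November. The period and the primary time point cannot both be met.

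This matters because six months is the time point of the primary comparison, and the sample size is built on changes over six months. If field teams worked to the stated calendar, an unplanned share of women would be measured early, at intervals that depend on when each entered. The result would still be reported as a six-month effect. Follow-up intervals cannot be corrected in the analysis once the interviews have been done.

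**Working it through.** **Inputs.** Baseline window 1 June to 24 July 2022, which is 30 + 24 = 54 days (Papers II and IV), or to 30 July, 60 days (Summary). Stated closes: December 2022 (Paper III), taken as 31 December, and November 2022 (Summary), taken as 30 November. Time point: six months. Two readings are mine. I take the preceding study to be the Paper II survey, because it supplies the participants. I take entry as uniform over calendar days, because the protocol gives no entry pattern.

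**Step 1: the plan's own period.** July to December is six calendar months long, so it fits only if every woman starts on 1 July. Even then 1 July + 6 months = 1 January 2023, which leaves no room for staggered entry or end-line visits.

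**Step 2: the plan's own rule.**
- 24 July + 6 months = 24 January 2023
- 30 July + 6 months = 30 January 2023

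Neither falls in December, so the stated period is not reproduced.

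**Step 3: share measured early if field work closed on the stated dates.** A woman is early if her entry date plus six months falls after the close. The share is early entry days divided by days in the window.

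| Window | Close | Calendar months | 182 days | 180 days |
|---|---|---|---|---|
| 1 June to 24 July | 31 Dec | 24/54 = 44.4% | 22/54 = 40.7% | 20/54 = 37.0% |
| 1 June to 30 July | 31 Dec | 30/60 = 50.0% | 28/60 = 46.7% | 26/60 = 43.3% |
| 1 to 24 July (July start) | 31 Dec | 24/24 = 100% | 22/24 = 91.7% | 20/24 = 83.3% |
| 1 June to 24 July | 30 Nov | 54/54 = 100% | 53/54 = 98.1% | 51/54 = 94.4% |

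If the intervention starts only once the survey is over (25 to 31 July), a 31 December close makes every woman early on all three counts.

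**Step 4: size of the shortfall.** Six months from 24 July is 184 days.
- Close 31 December: 160 days of follow-up, 184 − 160 = 24 days short. From 30 July: 154 days, 30 short.
- Close 30 November: 129 days, 184 − 129 = 55 days short. If week 0 fell on 24 July, the last supervised visit (week 15, day 105) would be only 24 days earlier.

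**Step 5: what removes it.** With a close on 31 January 2023 the early share is zero for every entry window above.

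**The case against.** The strongest reply is that no section gives a closing date for end-line. Paper III states a study period, while every section that describes the outcome puts it at or after six months. Table 4 has an end-line row and columns to February 2023. The likelier fault is then a wrong calendar label, not a plan to measure early. This stands, and it is why the percentages are conditional. It does not remove the contradiction, because the two stated periods still cannot hold the stated follow-up.

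A second reply uses the April to June interview dates. If the symptom-score baseline were taken then, every woman would have at least 184 days to 31 December. But six months of intervention from July would still not be reached, and Paper IV dates the quality-of-life baseline June to July. Those interview dates are one more entry to reconcile.

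Third, the wordings of the clock (from the initial visit, of intervention, of training) can share week 0 as origin, and visit windows are often left to an analysis plan. Both are fair. The training wording, however, gives no origin for controls, who are not trained.

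A reader might infer more than the protocol supports:

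- **That 44% is a minimum.** It depends on uniform entry, calendar months and a baseline clock. Day counts give less, and so would front-loaded entry.
- **That follow-up would run from about four to seven months.** No single close does this: 30 November gives 129 to 182 days, 31 December gives 160 to 213, for entry from 1 June to 24 July.
- **That end-line is one five-day round.** Table 5 has "End line assessment | Person | 8 | 359 | 5 days", but it lists paid days. The same table pays data collectors for 10 days and examiners for 30, against a 54-day baseline.
- **That follow-up would differ between arms.** No order of surveying kebeles is stated, and allocation is by lottery within strata.
- **That Table 4 is a third end date.** Its activity cells cannot be read in the text available, so only its column range is known.

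**Conclusion.** The stated period is wrong as written. On the protocol's own dates the last women reach six months on 24 to 30 January 2023, so neither the December nor the November end can deliver the primary time point. This part is calendar arithmetic, taking the preceding study as the Paper II survey.

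The consequence is conditional on field work closing on the stated dates. With uniform entry from 1 June and a 31 December close, about 37% to 50% of women would be measured early, the range reflecting how six months is counted and which baseline end date is used. With a July intervention start it is 83% to 100%. With a 30 November close it is essentially all (94% to 100%). The December shortfall is modest, at most about 24 days for a 24 July baseline; the November one is about 55 days. No effect on the treatment estimate has been quantified. Severity is modest, but the plan should be corrected before end-line field work is scheduled.

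**What to change.** 1. Restate the trial period in Paper III, Study Area and Period, and in the Summary so that it runs to at least 31 January 2023. Table 4 already has columns to February 2023. If the last week-0 visit falls later than 31 July, or the visit window extends beyond six months, move the end date by the same amount.
2. Reconcile the baseline dates in the Summary, in both places in Paper II, and in Paper IV, so that there is one survey window and one trial baseline.
3. In Paper III (Data Measurements, Data Collection Tools and Procedure, Data Management and Analysis) and in Paper IV (Data Collection Tools and Procedures), define end-line in the same words: six months after each woman's own week-0 visit, or first counselling visit for controls, within one visit window common to both arms. The investigators should choose the width of the window.

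The cost is protocol wording and a field-work close about one month later than Paper III now states. The number of interviews does not change.
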